## Background

Major concerns in oncology today are the rapidly increasing complexity of treatment, the steadily augmenting number of treatment lines that are administered, and new agents that increases the demand for anticancer treatment at end-of-life (EoL). Coupled with this is the increasing use of advanced imaging, i.e. computed tomography (CT) and positron emission tomography (PET) scans and magnetic resonance imaging (MRI). About one-third of the cost of cancer care is spent during the patient’s last year of life [1], and costs are expected to escalate rapidly, which threatens the sustainability of the present services [2, 3].

One article examined the rationale for discontinuation of chemotherapy for metastatic non-small-cell lung cancer (NSCLC) and identified a huge variability in these processes, unrelated to time of death [4], as addressed by others [5–7]. This is in spite of patients, families, and oncologists uniformly recognizing the administration of chemotherapy near death as aggressive and as an indicator of poor EoL care [8].

The American Society of Oncology (ASCO) has defined discontinuation of chemotherapy given with a life-prolonging intent in the last 2 weeks of life as a benchmark for improving clinical practice [9]. It is difficult to decide the optimal chemotherapy intensity during the last periods of life at an individual patient level. For example, if the treatment of choice in some patients with chemosensitive solid tumors is a therapy with modest side effects, a high response rate, and good symptom relief, this may be appropriate even if the life expectancy is < 3 months. However, a French registry-based study in > 279,000 patients found no clear pattern between the expected chemosensitivity of different solid cancers and the administration of chemotherapy at EoL [6].

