### Sample size

Sample size calculation was based on the primary endpoint: the proportion of patients who receive chemotherapy during their last 3 months of life (Table 1). This took into consideration the predetermined number of 12 as the total number of clusters, i.e. hospitals, that was chosen for contingency/feasibility reasons and allowing for intra-cluster correlation coefficient (ICC) in the range of 0.06–0.09, which is usually considered appropriate for process outcomes. In addition, calculations were performed to provide 80% power at the two-sided 5% level to detect a 25% difference in chemotherapy use between the two arms, i.e. 20% versus 45% in the treatment and control groups, respectively [61]. The choice of the clinically relevant treatment effect used for sample size calculation (25% difference for chemotherapy administration) was based on both clinical judgment and previous data [62, 63]. Effects on power increase due to adjustment by baseline measurements and other covariates (see statistical analysis section for the full list of covariates proposed) were also considered, allowing for correlation coefficient between outcome and adjustment covariates (r_adj_) up to 0.4. Table 2 reports sample size per treatment arm for various values of ICC and (r_adj_).

**Table 2 Tab2:** Sample size per treatment arm for various values of ICC and (r_adj_)

			**r**_**adj**_		
	*0.4*	*0.3*	*0.2*	*0.1*	*NO*^a^

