### Study population

#### Inclusion criteria: participant level

##### Patients

At the second level of the C-RCT, the following eligibility criteria apply to patient inclusion:
A verified metastatic or locally advanced cancer of the upper gastrointestinal (GI) tract, lower GI tract, pancreas, liver, breast, bladder, prostate, kidney, cholangiocarcinoma, or malignant melanoma;Defined as a patient in need of PC with an anticipated life expectancy of < 12 months;Scheduled to start the anticipated last line of chemotherapy (definition: tumor directed systemic therapy). Time of inclusion that is based on the decisions about last line of chemotherapy, varies by diagnosis, and is equivalent to first line in some diagnoses;Age > 18 years;Fluency in written and oral Norwegian;Physically and cognitively able to provide written consent, based on clinical criteria, e.g. not too frail or having signs of disorientation, confusion, attention deficit, poor coordination;Scheduled to receive all oncological and specialized palliative treatment at the participating hospital, i.e. residing in the local area of the including hospital;WHO performance status 0–2.

Because gynecological and lung cancer patients receive anticancer treatment at the departments of lung and gynecology in most hospitals, these diagnoses were not included.

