### The patient-centered care pathways

A PCCP in PALLiON means that the planned treatment trajectory for *the individual* patient is outlined and presented to the patient and caregivers shortly after inclusion in the study. The PALLiON pathways are easily accessible on all hospital and free-standing computers by a shortcut key, to the front page (Fig. 1). The pathways are developed for everyday clinical use in that they guide the physicians’ and other healthcare providers’ actions and responsibilities in the four sub-pathways depicted by the white arrows in Fig. 1. The content corresponds with national recommendations for treatment and follow-up for the respective diagnostic groups [75], and the former and updated national strategies for cancer in Norway [76, 77].

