##### Statistics

The design makes it possible to evaluate the effect of an early integration of oncology and PC at the institutional and patient levels across intervention and control arms, by comparing the use of chemotherapy in the last 3 months of life.

Analyses on the primary outcome will be performed when there are 300 patients in each arm with data on chemotherapy use in the last 3 months of life, which is the basis for the power estimation. Standard descriptive statistics will be used for background variables. Further, data will be analyzed by the intention-to-treat approach; mixed effect regression models will be used to analyze both primary and secondary endpoints in order to account for clustering. Logistic and linear regression models will be used respectively for binary and continuous outcomes and all models will be adjusted for potentially relevant baseline covariates at patient level, i.e. sex, age, diagnosis, performance status score, and baseline symptom scores. The analysis of the main outcome will also be adjusted by size of the catchment areas, which is the randomization stratification factor.

Survival analysis methods, i.e. Kaplan–Meier curves and Cox proportional hazards models with shared frailty terms to account for clustering and Kaplan–Meier curves, will be employed in order to model time to death. Sensitivity analyses to different methods will be applied to handle missing data in the secondary PROs: complete case analysis and multiple imputations. This also applies to patient- and caregiver-reported outcomes. Paper forms will be used to collect medical data and PROs for comparisons across arms.

Further, a potential effect of the intervention at each of the centers in the intervention arm may be evaluated at a later stage as an explorative outcome by comparing post-intervention data with historical data, e.g. on use of chemotherapy and number of readmissions/emergency admissions in the very last stages of life as appropriate.

The CONSORT recommendations for reporting RCTs will be followed. The CONSORT recommendations for reporting C-RCTs will be followed. IBM SPSS Statistics for Windows, version 25.0 (IBM Corp., Armonk, NY, USA) and STATA (Stata Corp. LCC, College Station, TX, USA) will be used.

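### The optional per-centre comparison with historical data is labelled an intervention effect, but it can only show change over time at the intervention hospitals

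*Protocol article*

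**What the plan says.** The trial's main comparison, set out in the Statistics section of the protocol article, is randomised. Use of chemotherapy is compared "across intervention and control arms, by comparing the use of chemotherapy in the last 3 months of life", by intention to treat, with mixed-effects models and covariate adjustment.

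Later in the same section a separate, optional analysis is described: "a potential effect of the intervention at each of the centers in the intervention arm may be evaluated at a later stage as an explorative" endpoint. The method given is a before-after contrast, "by comparing post-intervention data with historical data, e.g. on use of chemotherapy and number of readmissions/emergency admissions", close to death and where suitable.

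Three things are fixed there: the label (an effect of the intervention), the hospitals (those in the intervention arm) and the comparator (historical data). No test, significance level, historical period, historical sample size or case definition is given. The analysis is not among the exploratory objectives in Table 1, which lists survival and direct costs.

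**The concern.** Comparing a hospital with its own past asks whether anything changed there. It answers whether the intervention changed anything only if nothing else moved the outcome between the periods and the two groups of patients are alike. The document gives reason to doubt both conditions.

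- **Calendar change.** The Background refers to "the steadily augmenting number of treatment lines that are administered, and new agents that increases the demand for anticancer treatment at end-of-life (EoL"). The pathway section mentions "the former and updated national strategies for cancer in Norway", which shows that policy moved, though not that chemotherapy use did. Recruitment alone runs from March 2017 to the end of 2020.
- **Patients.** Trial patients must be "Scheduled to start the anticipated last line of chemotherapy", have WHO performance status 0–2, give consent and not already be followed in a palliative care programme. Nothing in the Statistics section requires the same of historical patients.

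Six randomised control hospitals live through the same calendar period, but this analysis does not use them. A reader could take the six per-centre results as evidence of where the intervention worked or failed, when they may show only drift or case mix.

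**Working it through.** **1. The plan's own figures.** The document states no figure for the before-after comparison. Its sample size supplies the base rate and the hospital sizes, so I checked that first. Inputs (Sample size section): 20% versus 45%, two-sided 5%, 80% power, 6 hospitals per arm, ICC 0.08, r_adj 0.1.

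- Individually randomised n per arm, using t with 10 df for alpha: (2.228 + 0.842)² × (0.20×0.80 + 0.45×0.55) / 0.25² = 61.44.
- After covariate adjustment: 61.44 × (1 − 0.1²) = 60.83.
- Patients per hospital: 60.83 × 0.92 / (6 − 60.83 × 0.08) = 49.4, rounded up to 50. Six hospitals give 300 per arm, as stated.
- Table 3 plans 85, 50 and 35 patients per large, medium and small hospital. After 12% attrition these are about 75, 44 and 31.

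**2. What the contrast estimates.** Post-intervention rate minus historical rate = intervention effect + calendar change + difference in patients. With data from one hospital, the three terms cannot be separated.

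**3. Illustration with zero intervention effect.** My assumptions: historical rate p0 = 45% (the plan's control rate), later rate p1 shifted by drift alone, trial patients as the post-intervention sample, historical n equal to trial n, and a pooled two-proportion z-test at two-sided 5%.

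With d = p0 − p1 and p̄ = (p0 + p1)/2, let c = 1.96 × √(2p̄(1−p̄)/n) and s = √((p0(1−p0) + p1(1−p1))/n). Then P(reject) = Φ((d−c)/s) + Φ((−d−c)/s).

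Example, n = 44 and a 10-point fall: c = 1.96 × 0.1044 = 0.2047 and s = 0.1039. P = Φ(−1.008) + Φ(−2.93) = 0.157 + 0.002 = 15.9%.

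| n per period | No drift | 5-point fall / rise | 10-point fall / rise |
|---|---|---|---|
| 31 | 5.0% | 6.8% / 6.8% | 12.5% / 12.2% |
| 44 | 5.0% | 7.6% / 7.5% | 15.9% / 15.4% |
| 75 | 5.0% | 9.5% / 9.4% | 23.8% / 23.1% |
| 35 | 5.0% | 7.0% / 7.0% | 13.5% / 13.2% |
| 50 | 5.0% | 8.0% / 7.9% | 17.4% / 16.9% |
| 85 | 5.0% | 10.1% / 10.0% | 26.4% / 25.5% |

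Enumerating the binomial outcomes exactly for the same test gives 6–11% for 5 points and 12–27% for 10 points. A history five times larger raises the 10-point-fall figures to about 35%, 22% and 17% for n = 75, 44 and 31.

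**4. Six looks.** With no drift, six unadjusted 5% tests give at least one rejection with probability 1 − 0.95⁶ = 26.5%. With a 10-point fall and n = 75/44/31 this becomes 69%. The first 26 points or so come from multiplicity, not from the before-after design.

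**5. The direction that the Background suggests.** Suppose a true effect of 45% to 20%, but a historical rate of 35% because use has risen since. Per-centre power for n = 75, 44 and 31 falls from 91%, 71% and 56% to 54%, 35% and 26%. A real benefit is partly hidden.

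**6. Ordinary hospital-by-period variation.** With no average drift, but 20% of the ICC 0.08 variance assumed specific to the period (SD = √(0.08 × 0.2475 × 0.2) = 0.063), simulation gives about 11–21% per centre.

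**7. Using the control hospitals.** In simulation, the change in six intervention hospitals minus the change in six control hospitals (t, 10 df) rejected in 4.6–5.3% of null runs for every drift from 0 to 15 points. This assumes that drift is common to both arms. It concerns the pooled effect and does not validate an effect for any single centre.

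**The case against.** The strongest reply is that this is one permissive sentence in a condensed article. The analysis may be done, later, as an explorative outcome, on examples of variables, as appropriate. No test is specified, so talk of rejection is the reviewer's addition. Neither the historical patients nor the post-intervention data are defined. The eligibility criteria could be applied to old records, and the later data might be hospital-wide and not limited to enrolled patients. The documents give no size of drift. At 5 points, per-centre rejection is barely above nominal.

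Most of that stands. A reader might infer that the trial plans a test that will often find an effect where there is none. The documents do not support this: the analysis is neither committed to nor specified as a test, and frequent rejection needs large drift, a large history, period variation or several unadjusted looks, all of which are assumptions. A reader might also infer that the likely error is a false success. The only trend in chemotherapy demand that the Background describes is upward, which points to masked benefit or apparent harm. Nor do the documents establish that historical patients would be unscreened, only that nothing requires them to be comparable.

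What the reply does not remove is the label. The sentence chooses the hospitals and the comparator and calls the result an effect of the intervention. That is a stated interpretation, not a detail left to an analysis plan, and exploratory status does not make an uncontrolled change an effect.

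**Conclusion.** The point holds as a minor one. Comparing intervention hospitals with their own history cannot separate an intervention effect from calendar change or case mix, so it should not carry that name. The illustrative rates of about 6–11% (5-point shift) and 12–27% (10-point shift) per centre rest on the assumed drift, the 45% base rate, equal-sized history, Table 3 numbers with or without attrition, and a conventional 5% test. None of them is an error rate of an analysis that the protocol specifies. The randomised primary and secondary comparisons and the sample size do not depend on this sentence.

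**What to change.** In the Statistics section of the protocol article, replace the reference to an effect of the intervention at each centre with *change over time at each intervention hospital*, and state that no claim of effect will be drawn from it. This costs one sentence and gives up the per-centre effect claim.

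If an effect estimate is wanted, and the same historical variables can be extracted at the control hospitals under one case definition applied to both periods, report the pooled change in intervention hospitals minus the change in control hospitals, with hospital-by-period variation in the error term. Show per-centre changes only descriptively, beside the control hospitals' change. This needs record extraction at six more hospitals, which is more than a wording change. The interval will also be wider than for a simple before-after comparison, and the estimate still relies on drift being common to both arms.

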### Data collection, patient registrations

A consensus-based set of key variables to describe or classify a PC cancer population has been requested for years and resulted in the EAPC Basic Dataset published in 2019 [68]. The second to final version of this dataset is used in this study, without grading of dementia, chronic obstructive pulmonary disease, and heart failure.

### Patient-reported outcome measures

Patient- and caregiver-reported data are collected on paper forms, sent by mail from the Trial Office every other month (Table 4). Returned forms will be stored there according to confidentiality regulations.

### The EAPC basic dataset: background information and symptoms

This part of the patient form is similar to the EAPC basic dataset [68] with a few adaptations to the present study. The form contains 14 questions: sociodemographic variables, i.e. date of birth, date of consent, and marital, living, educational, and working status, followed by ethnicity, use of tobacco and alcohol, and five questions on height and weight, nutritional status, and intake modified from the SGA [71]. For subsequent forms, one question about use of healthcare services since inclusion has been added, whereas general background items that are unlikely to change between assessments have been dropped, to reduce respondent burden.

This form contains 12 frequent cancer-related symptoms: pain; drowsiness; tiredness; nausea; appetite; dyspnea; depression; anxiety; wellbeing; sleep; constipation; and vomiting. The period is right now, and patients are asked to rate the intensity on a NRS of 0–10 (0 = no pain/no dyspnea, etc. to 10 = worst imaginable pain/dyspnea, etc.).

### EORTC QLQ-C15-PAL

The QLQ-C15-PAL [73] is a shortened version of the EORTC QLQ-C30 [81], one of the most widely used QoL questionnaires in oncology. Because the QLQ-C30 contains 30 items, was not initially developed for use in PC, and some of its content has been perceived as inappropriate by patients receiving PC, the QLQ-C15-PAL was developed, is well-validated and cross-culturally adapted, and is considered a core PC questionnaire. The QLQ-C15-PAL includes those elements of the QLQ-C30 identified as most relevant and important for PC, i.e. physical and emotional function, pain, fatigue, nausea/vomiting, appetite, dyspnea, constipation, sleeping difficulties, and overall QoL. All but the QoL item are scored on categorical scales from 1 (not at all) to 4 (very much) and transformed to a scale of 0–100. The Norwegian version has been validated and used in several PC studies [63, 82, 83].

### QLQ-INFO25

The QLQ-INFO25 (European Organisation of Research and Treatment of Cancer Quality Questionnaire-Information) [84] was developed to evaluate cancer patients’ perception of information received during different phases of care and has been cross-culturally validated according to the EORTC guidelines for module development [85]. The module has four multi-item scales—information about the disease (four items), medical tests (three items), treatment (six items), and other services (four items)—and eight single items, scored on categorical scales from 1 (not at all) to 4 (very much) and transformed to scales of 0–100. For the purposes of PALLiON, we have decided to delete one single item regarding sexuality as this may be perceived as inappropriate by patients in the last stages of life. The psychometric properties of the QLQ-INFO25 were confirmed, demonstrating a reliable and valid self-reported instrument. All items can be combined to generate a single score (α > 0.90). The module discriminated among groups based on gender, age, education, levels of anxiety and depression, information wishes and satisfaction, and was well suited for cross-cultural observational and intervention studies and together with, for example, the QLQ-C15-PAL scale.

### PHQ-9

Depressive symptoms will be assessed using the PHQ-9 [72], a self-report questionnaire commonly used in medically ill samples [4, 86, 87], and has proven good validity and sensitivity. The nine PHQ-items correspond to the DSM-5 diagnostic criteria for major depressive disorder and assess the frequency at which the symptoms have been bothersome during the past two weeks: 0 = “not at all”; 1 = “several days”; 2 = “more than half the days”; and 3 = “nearly every day”. To be classified as depressed according to the DSM-5 criteria, five out of nine criteria, including anhedonia and/or depressed mood, have to be present and scored as bothersome for at least “more than half the days” or “on some days”.

### GAD-7

The Generalized Anxiety Disorder 7-item (GAD-7) questionnaire is based on the DSM criteria for a generalized anxiety disorder [88]. It consists of seven items on general anxiety commonly experienced by cancer patients, such as tension and worrying in the past 2 weeks, scored on a 4-point Likert scale (0 = not at all, 3 = almost every day). The total score is in the range of 0–21. GAD-7 has been shown to have good reliability, as well as good criterion, construct, factorial and procedural validity, with a suggested cut point that optimized sensitivity (89%) and specificity (82%). GAD-7 is not defined as an outcome in PALLiON, but the items in GAD-7 address frequently experienced psychological symptoms in patients with cancer, which is the rationale for choosing this instrument.

### Caregiver-reported outcome measures background variables

This baseline caregiver form has eight variables concerning sociodemographic variables, i.e. date of birth, date of consent, marital, living, level of education and working status, relation to patient, and current chronic diseases. These variables are not included in subsequent caregiver forms.

### FAMCARE

Although patient satisfaction with care has been shown to be amenable to change with PC interventions, only a few intervention studies have demonstrated a positive effect of specific PC interventions on caregivers’ health and QoL [17, 21]. The Family Satisfaction with End-of-Life Care (FAMCARE) scale [89] is a 20-item self-report measure that was developed to measure family satisfaction with PC for cancer. The questionnaire asks for the degree to which family members are content with the healthcare provider behaviors directed toward the patient and themselves and can be administered during the disease trajectory or at some point after a patient’s death. A Norwegian C-RCT showed that caregivers to patients with cancer receiving specialized PC reported higher satisfaction with EoL care on FAMCARE than caregivers in the control group [21].

### SF-36

SF-36 is a brief, yet comprehensive generic measure of subjective health and QoL [90]. The 36 items can be summed into eight multi-item scales measuring physical functioning, bodily pain, general health perception, mental health, role limitations due to physical problems, role limitations due to emotional problems, social function, and vitality. An additional item reports health transition over the past year. Items are scored and transformed to scales of 0–100 for ease of interpretation. Extensive reference data exist from Norwegian population surveys [91, 92], facilitating comparisons across populations.

In line with the definition of PC, caregiver follow-up is essential. As we believe in the study’s beneficial effects on caregiver perception of care, we will follow the caregiver twice after the patient is dead. The questionnaire packet will be sent by mail at 6 and 12 months after the patient’s death, with a specific consent form inserted.

